## Materials and methods

### Study hypothesis and primary outcome

The primary hypothesis of this study is that the SGLT-2 inhibitor is superior to other oral hypoglycemic medications for rhythm control in patients with AF and DM, diagnosed within the prior year. A step-up treatment will be carried out when the participant’s AF recurs. The recurrence rate of AF will be investigated after performing stepwise rhythm control therapies including anti-arrhythmic drugs (AAD) and ablation. AF is defined as per the 2019 AHA/ACC/HRS Guideline, i.e., irregular R–R intervals (when atrioventricular conduction is present), absence of distinct repeating P waves, and irregular atrial activity [20]. It is checked by 24-h Holter ECG every 3 months and is considered significant when it lasts for > 30 s [21].

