**Fig 2 pone.0280359.g002:**
[figure not shown]
Flow chart of the trial. Brief flow of the BEYOND trial described as a schematic diagram. Patients who enroll this trial will be randomly administrated SGLT-2 inhibitor or other DM medication while applying stepwise rhythm control strategy for AF.

Patients diagnosed with AF within a year, who have never undergone any ablation treatment, newly diagnosed with DM, and with ages between 18 and 80 years will be selected as the study participants. They will be enrolled in 7 tertiary medical centers from the Division of Cardiology and the Division of Endocrinology. As patients diagnosed with AF also tend to check for DM to calculate the CHAD2-VASc score, those who have been diagnosed as AF in the prior year and newly diagnosed with DM in the follow-up can be recruited for the trial in the Division of Cardiology. To identify patients for enrollment in the Division of Endocrinology, every patient newly diagnosed with DM during the enrollment period will be asked for 12-lead ECG and 24-h Holter ECG; those with AF > 10 s in 12-lead ECG or >30 s in 24-h Holter ECG can be recruited for the trial. All participants must meet the required inclusion (Table 3) and exclusion criteria (Table 4) at the point of randomization. The participants should otherwise be healthy and use only oral hypoglycemic agents, not subcutaneous agents, for glycemic control.

**Table 3 pone.0280359.t003:** Inclusion criteria.

• At least one episode of AF* that is documented during the prior year by any kind of ECG recording. • Type 2 DM was diagnosed (HbA1c > 6.5%) and the patient was using oral hypoglycemic agents only for glycemic control. • At least 18 years old, but not older than 80 years. • Normal ECG parameters, measured in sinus rhythm (QRS width ≤ 120 ms, QTc interval < 440 ms, and PQ interval ≤ 210 ms in a 12-lead ECG). • Be able and willing to give informed consent.

*AF episode must last longer than 30 s on single ECG, 10 s on 12-lead ECG or 24-h Holter ECG.

AF, atrial fibrillation; DM, diabetes mellitus; ECG, electrocardiogram.

**Table 4 pone.0280359.t004:** Exclusion criteria.

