## Discussion

Recently, SGLT-2 inhibitors have been shown to exhibit beneficial effects beyond glucose control. SGLT-2 inhibitors were originally developed as hypoglycemic agents. They target SGLT-2 protein, which is responsible for 90% reabsorption of filtered glucose in the proximal convoluted tubules of the kidneys [35], resulting in diuresis. Previous studies have shown that SGLT-2 inhibitors suppress sympathetic overactivity [36] and oxidative stress [37]. DAPA-HF and EMPEROR-Reduced trial demonstrated that SGLT-2 inhibitors can reduce cardiovascular mortality in patients with HF [14,15]. Considering that AF and CHF are mutual risk factors, we designed a clinical trial based on the rationale that SGLT-2 inhibitors might be able to improve the clinical outcome of AF with DM by establishing the rhythm control of AF.

We will compare the recurrence rate of AF of the two groups after performing AAD administration and hypoglycemic treatment for at least 3 months as a primary outcome and evaluating the degree of rhythm control of AF. Because enlisting patients who were previously diagnosed with DM and whose glucose levels are currently well controlled in the trial can give rise to grave ethical issues, we recruited patients newly diagnosed with AF or DM within 1 year. We decided not to choose any specific SGLT-2 inhibitor agents and their dosage right away; instead, we decided to recommend physicians to utilize the maximum tolerable doses.

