The trial has some limitations as well. First, it primarily focuses on the effect of SGLT-2 inhibitors in patients newly diagnosed with AF and DM within 1 year. As a result, long-term effects of SGLT-2 inhibitors cannot be analyzed in this trial. Nonetheless, the short-term effects of SGLT-2 inhibitors are meaningful because these inhibitors reduced the incidence of atrial arrhythmia within 1 year compared to that in the control group [32] and the diuretic effect of SGLT-2 inhibitors appeared to be most prominent in first three months of administration only [48]. Second, a certain SGLT-2 inhibitor product is not unified in this trial. Physicians can choose the specific product and the maximum tolerable dose based on their clinical decisions and settings. To control the bias, a subgroup analysis including stratification on products will be conducted as post-hoc analysis.

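### The eligibility statements conflict on AF onset: the Table 3 line asks only for an AF episode recorded in the prior year, while the hypothesis is about AF diagnosed in that year

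*Protocol article*

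**What the plan says.** The Protocol article describes the AF population in several places.

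- **Study hypothesis and primary outcome:** superiority is claimed "for rhythm control in patients with AF and DM, diagnosed within the prior year". The Abstract describes the 716 patients in the same way, as new AF and new DM within one year.
- **Study design and participants, opening text:** "Patients diagnosed with AF within a year, who have never undergone any ablation treatment, newly diagnosed with DM" are to be selected.
- **Same section, Cardiology route:** "those who have been diagnosed as AF in the prior year and newly diagnosed with DM in the follow-up can be recruited".
- **Same section, Endocrinology route:** among patients with new DM, "those with AF > 10 s in 12-lead ECG or >30 s in 24-h Holter ECG can be recruited for the trial".
- **Same section, binding rule:** "All participants must meet the required inclusion (Table 3) and exclusion criteria (Table 4) at the point of randomization".
- **Table 3, AF line:** "At least one episode of AF* that is documented during the prior year by any kind of ECG recording".
- **Table 4:** the only exclusion tied to AF history is a previous ablation.
- **Discussion, rationale:** "we recruited patients newly diagnosed with AF or DM within 1 year".
- **Discussion, limitations:** the trial is about the drug effect "in patients newly diagnosed with AF and DM within 1 year".

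**The concern.** An episode documented in the past year is not a diagnosis made in the past year. Someone with AF for ten years and one recorded episode last month meets the Table 3 line and, if never ablated, is not removed by any AF-related line in Table 4. If a centre screens from the tables, that patient can be randomised although the hypothesis excludes them.

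By the article's own reasoning, AF duration matters for the primary outcome. The Secondary outcomes section and the Discussion argue that AF progressively remodels the left atrium and that remodelling promotes further AF. Patients with older AF may therefore recur at a different rate from those the trial says it studies. At stake are the population to which the result applies and possibly the size of the effect. With several centres recruiting through two divisions, the looser and the stricter rule could also be applied differently by site.

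**Working it through.** **Step 1. Compare the statements on AF onset.**

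| Place | AF requirement | First diagnosis within one year? |
|---|---|---|
| Abstract | new AF and DM within one year | yes |
| Hypothesis | AF and DM diagnosed in the prior year | yes |
| Opening recruitment text | AF diagnosed within a year | yes |
| Cardiology route | AF diagnosed in the prior year | yes |
| Endocrinology route | AF on the screening ECG or Holter | not asked |
| Table 3 | at least one episode documented in the prior year | not asked |
| Table 4 | no previous ablation | not asked |
| Discussion, rationale | AF *or* DM new within one year | not required if DM is new |
| Discussion, limitations | new AF and DM within one year | yes |
| Conclusions | AF and DM, no time limit | not stated |

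**Step 2. Apply the tables to a test patient.** Take ten years of paroxysmal AF, never ablated, one episode on ECG last month, now in sinus rhythm, with type 2 DM treated only with oral agents, and meeting every other line.

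- Table 3, AF line: met. Table 3, ECG parameters in sinus rhythm: can be met.
- Table 4, previous ablation: does not apply.
- Opening recruitment text and hypothesis: not met.

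The tables and the text therefore give different answers for the same patient. If this patient's DM is found at an Endocrinology clinic and the screening Holter shows AF, that route also accepts them.

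**Step 3. Can the consequence be sized?** Not from the documents. They give 716 patients (358 per arm), 10% loss, a 40% reduction, 80% power and 5% alpha. They give no control recurrence rate, no expected share of older AF and no effect by AF duration. The following is illustration only.

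- Evaluable per arm: 358 × 0.9 = 322.
- Power = Φ{[|p₁ − p₂|√n − 1.96√(2p̄(1 − p̄))] / √[p₁(1 − p₁) + p₂(1 − p₂)]}, where p̄ is the mean of p₁ and p₂.
- The control rate giving 80% power at relative risk (RR) 0.60 is back-solved as 20.3% against 12.2%: [0.0813 × 17.94 − 1.96 × 0.5220] / 0.5188 = 0.84, and Φ(0.84) = 0.80.
- Let a share f have older AF, with RR r in that group and the same control rate. Pooled RR = 0.60(1 − f) + r·f.

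| Assumed f | Assumed r | Pooled RR | Power, control 20.3% | Power, control 50% |
|---|---|---|---|---|
| 0 | – | 0.60 | 80% | >99% |
| 0.2 | 0.8 | 0.64 | 70% | >99% |
| 0.3 | 0.8 | 0.66 | 65% | 99% |
| 0.2 | 1.0 | 0.68 | 59% | 99% |
| 0.3 | 1.0 | 0.72 | 48% | 95% |

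If older AF instead has twice the 20.3% control rate, power for f = 0.2 to 0.3 is 73% to 70% at r = 0.8, and 52% to 40% at r = 1.0. The answer is set by the assumptions: power runs from 40% to above 99%.

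**The case against.** The strongest reply is that Table 3 does not stand alone. The opening sentence of the same section is itself an eligibility statement and restricts entry to AF diagnosed within a year, and the Cardiology route repeats it. Requiring everyone to meet the tables makes them necessary; it does not make them sufficient or cancel the text above them. Read together, the section can mean AF diagnosed within a year and confirmed by ECG. This stands: a reader might infer that patients with long-standing AF plainly qualify, but the documents support only that the passages conflict.

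Three further limits also stand.

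- The sinus-rhythm ECG line makes entry harder for patients in continuous AF. It need not exclude them all, since the rhythm-control strategy foresees cardioversion of persistent AF. The gap mainly concerns ablation-naive patients with a long history who can show sinus rhythm.
- The *or* in the Discussion sits in a remark on why patients with established, well-controlled DM are not enrolled, and the Abstract, hypothesis and limitations all say *and*. It adds to the inconsistency but does not by itself establish a rule admitting older AF.
- The remodelling argument links AF progression to recurrence. Nothing in the article says that SGLT-2 inhibitors work less well in older AF, so dilution is possible, not shown.

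What does not stand is that the reply removes the problem. A limit placed in the narrative and absent from the listed criteria can be missed at screening, and the Endocrinology route has no explicit check that AF is new.

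**Conclusion.** The inconsistency is real and should be corrected. Applied as a checklist, the listed criteria accept some patients outside the population of the primary hypothesis. The finding rests on the text alone and needs no numerical assumption.

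Randomisation is 1:1, so a mixed population does not bias the comparison between arms. The harm is that the result may not describe the recent-onset population named in the hypothesis, and that the effect may differ from the one planned for.

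Two stronger readings should be avoided. A reader might infer a definite loss of power, but the share of older AF, its RR and the 20.3% control rate are all assumed or back-solved, and at a 50% control rate power stays at about 95% or above in the cases with equal base rates. A reader might also infer a mismatch with the trial's conclusions, but the Conclusions section speaks of AF and DM without a one-year limit.

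**What to change.** 1. Reword the AF line in Table 3 so that the first AF diagnosis, meaning the first ECG-documented episode, falls within the year before randomisation, as the hypothesis already states.
2. Apply the same condition to both recruitment routes, so that Endocrinology also checks whether AF was already known.
3. Change *or* to *and* in the Discussion, to match the Abstract, hypothesis and limitations.
4. Record the date of first AF documentation on the case report form.
5. If patients with older AF were already enrolled, add a supporting analysis of the primary outcome in those who meet the stated population. Date of onset is a baseline characteristic, so the comparison in that subset remains randomised, with less precision.

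The cost is one eligibility line, one date field and matching text edits. Recruitment may be slightly slower because older AF is no longer accepted at any site.

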### Secondary outcomes

Secondary outcomes are listed in Table 1. AF-free survival will be compared between the two groups as the first of the secondary outcome, analyzed using the Kaplan–Meier method, and documented on curve. AF burden at 3-month follow-up visit, 12-month follow-up visit in those who did not step up and used AAD only for rhythm control, immediately before trying ablation, and at 12-month follow-up visit in those who stepped up and underwent ablation in both the SGLT-2 inhibitor group and the control group will be compared. AF burden is defined as the atrial fibrillation time percentage documented on 24-h Holter ECG [22]. Ablation rate, which is the percentage of patients undergoing ablation, within a year will also be compared between the two groups to identify the efficacy of symptom and rhythm control using SGLT-2 inhibitors. Sinus rhythm is considered stable when either a standard ECG or a 24-h Holter ECG showed no episode of clinically relevant arrhythmia, including AF, at the time of check-up [23]. The proportion of participants with stable sinus rhythm in all participants, regardless of with or without ablation, is compared between the two groups at baseline, 6-, and 12-month follow-up visits.

**Table 1 pone.0280359.t001:** Secondary outcomes.

• Rhythm control • AF-free survival • AF burden at • 3-month F/U visit, 12-month F/U visit in those who did not step up to session 2 • Immediately before trying ablation, 12-month F/U visit in those who stepped up to session 2 • Percentage of patients undergoing ablation within a year • Sinus rhythm maintenance* • Diameter of LA • NT-proBNP • Symptom score (EHRA score) • Quality of life (EQ-5D, SF-12)

*Defined as the absence of clinically relevant arrhythmia (e.g., AF, AFL, sustained VT, and VF).

AF, atrial fibrillation; LA, left atrium; F/U, follow up; NT-proBNP, N-terminal pro-B-type natriuretic peptide; EHRA, European Heart Rhythm Association; EQ-5D, EuroQol-5 Dimension; SF-12, Short Form-12 Health Survey Questionnaire; AFL, atrial flutter; VT, ventricular tachycardia; VF, ventricular fibrillation.

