**Fig 1 pone.0280359.g001:**
[figure not shown]
Completed SPIRIT schedule of trial. The rough schedule of BEYOND trial is summarized in a table. If AF is recurred during the follow-up period, patient will get a catheter or CRYO-balloon ablation and have an additional one-year follow-up period after ablation.

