The rhythm control strategy for AF will be followed, independent of the type of hypoglycemic agents received. This strategy includes two sessions (Fig 2). In session 1, an AAD will be assigned to every participant and taken for at least 3 months. If patients have persistent AF, cardioversion will be performed with AAD. During the follow-up, those with recurrent AF should step up to session 2, which involves treatment with radiofrequency ablation (RFA) or CRYO-balloon ablation (4 pulmonary vein isolation; 4PVI). For participants of session 2, the follow-up will begin with the moment RFA or cryotherapy is applied, which will be regarded as 0-month; follow-up will be conducted every 3 months for the next 12 months. The rhythm control strategy will be conducted as per the clinical guidelines of 2020 ESC [30] and 2019 AHA/ACC/HRS guidelines [20] for AF.

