### Follow-up and detection of AF recurrence

After their recruitment, the participants will receive baseline and evaluation studies under scrutiny, which include history taking, physical examination, blood sampling, urine sampling, 12-lead ECG, 24-h Holter ECG, TTE, EHRA, EQ-5D, and SF-12. The follow-up schedule will begin with the prescription of oral hypoglycemic agents (Table 5). During each intervention, the following steps were conducted: (1) history taking for the review of AF and DM status, adverse events, and other specific illnesses on every visit; (2) physical examination to evaluate any DM complication, AF, NYHA score, neurologic exam, systolic and diastolic blood pressure; (3) blood sampling for CBC, BUN/Cr, electrolyte, coagulation profile, HbA1c, fasting glucose, AST/ALT, lipid battery, and NT-proBNP; (4) urine sampling for dip stick urinalysis with microscopy and measuring proteinuria (especially for albuminuria); and (5) TTE to measure the LA size and left ventricular ejection fraction (LVEF). Any other additive assessing procedure may be conducted and recorded during the clinical course of the patients.

**Table 5 pone.0280359.t005:** Data-collection requirements.

Investigation	Baseline	3M	6M	9M	12M
Inclusion/Exclusion criteria	X				
Medical History	X	X	X	X	X
Physical Examination	X	X	X	X	X
12-lead ECG	X	X	X	X	X
24-h Holter ECG*	X	X	X	X	X
Blood, Urine sample	X				X
Transthoracic Echocardiography (TTE)	X				X
NT-proBNP	X				X
EHRA Score	X	X	X	X	X
EQ-5D, SF-12	X				X
Adverse Events History**		X	X	X	X

*Patients with an ablation (RFA or 4PVI) will be monitored every 3 months that point on for an additional year.

**To evaluate adverse events, any suitable diagnostic investigation can be performed.

Abbreviations. ECG, electrocardiogram; NT-proBNP, N-terminal pro-B-type natriuretic peptide; EHRA, European Heart Rhythm Association; EQ-5D, EuroQol-5 Dimension; SF-12, Short Form-12 Health Survey Questionnaire.

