### Statistical plan, sample size, and power determination

In this study, 716 patients will be enrolled from 7 tertiary medical centers. The sample size was determined based on the primary outcome, i.e., the SGLT-2 inhibitors should show 40% reduction in AF after a year of treatment [32] and 50% of AAD users should step up to the ablation therapy [33,34]. Assuming 10% follow-up loss, the sample size of 716 patients (358 in each group) is expected to achieve 80% power and an alpha-level of 5% to detect the difference. The study is powered to demonstrate the superior additive effect of SGLT-2 inhibitors over other hypoglycemic agents using the Chi square method. AF recurrence rate and ratio of sinus rhythm on 24-h holter EKG will be analyzed using Chi square test, and left atrial size, NT-pro BNP and quality of life (AFEQT) score on 12-month final follow-up will be analyzed by student t-test. Disease-free survival and overall survival during the follow-up period will be calculated using Kaplan-Meier method. Mono-variable and multi-variable cox regression analysis will be used to calculate hazard ratio of SGLT-2 group.

To reduce the selection bias, all subjects will be randomized to allocate the hypoglycemic agents according to random number table. Missing data is planned to be controlled using multiple imputation.

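### Two definitions of month 0 for ablated patients leave the timing of the pooled secondary outcomes ambiguous

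*Protocol article*

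**What the plan says.** The Protocol article gives two starting points for follow-up.

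- Study design and participants, in the paragraph on the two-session rhythm control strategy, says that for session 2 patients "the follow-up will begin with the moment RFA or cryotherapy is applied, which will be regarded as 0-month", with visits every 3 months over the following 12 months.
- Follow-up and detection of AF recurrence says: "The follow-up schedule will begin with the prescription of oral hypoglycemic agents (Table 5". No exception is made for ablated patients. The footnote to the Holter row of Table 5 adds: "Patients with an ablation (RFA or 4PVI) will be monitored every 3 months that point on for an additional year". The text below the table repeats this for Holter only. Echocardiography, NT-proBNP, EHRA score and EQ-5D/SF-12 have no post-ablation schedule.
- The Fig 1 caption says that patients with recurrence will be ablated and "have an additional one-year follow-up period after ablation".

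Several outcomes are then compared by arm at labelled visits. Under Secondary outcomes, stable sinus rhythm "in all participants, regardless of with or without ablation, is compared between the two groups at baseline, 6-, and 12-month follow-up visits". The same section sets EHRA score at 3, 6, 9 and 12 months, and left atrial diameter, NT-proBNP and EQ-5D/SF-12 at 12 months. In the statistical section, left atrial size, NT-proBNP and quality of life "on 12-month final follow-up will be analyzed by student t-test".

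**The concern.** The article does not say which of the two clocks the labels 6-month and 12-month refer to once a patient has been ablated. One site could do the 12-month echocardiogram a year after first prescription, and another a year after ablation. Both would have followed the article.

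If the reset is followed, the time of assessment depends on an event after randomisation that the treatment is meant to influence. Ablation follows AF recurrence, and the article compares the ablation rate between arms as a sign of efficacy. The trial is also open-label and ablation is at the physician's discretion, so ablation rates could differ for other reasons too. Time since randomisation and length of drug exposure at the same labelled visit could then differ between arms, and randomisation would not protect against that.

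The choice also cannot be repaired at analysis. An echocardiogram, blood sample or questionnaire not obtained at month 12 from randomisation cannot be recovered later.

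**Working it through.** The article states no figure for visit timing, so there is none to reproduce. The sample size of 716 is not in question here.

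**Inputs from the article**
- Earliest ablation: about month 3, since the antiarrhythmic drug is taken for at least 3 months (Study design and participants).
- Latest ablation considered: month 12, the end of the Table 5 schedule.
- 358 patients per group, 50% of antiarrhythmic drug users stepping up to ablation, and a 40% reduction in AF (statistical section).

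**Assumptions, not in the article**
- Randomisation and first prescription fall at about the same time.
- Ablation rates by arm are 50% (control) and 30% (SGLT-2 inhibitor). This treats the 50% as the control rate and applies the 40% reduction to ablation: 0.50 × (1 − 0.40) = 0.30.
- Mean time of ablation is the same in both arms.

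**Step 1: one patient.** With ablation at month m, a visit labelled k months on the reset clock falls at m + k months after randomisation.
- 6-month visit: 3 + 6 = 9 to 12 + 6 = 18 months.
- 12-month visit: 3 + 12 = 15 to 12 + 12 = 24 months.
- Example: ablation at month 4.5 gives visits at 7.5, 10.5, 13.5 and 16.5 months. If the reset replaces the Table 5 schedule, this patient has no visit at 6 or 12 months from randomisation, and the 12-month echocardiogram comes at 16.5 months. If Table 5 stands, it comes at 12 months.

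**Step 2: the arms.** With p the proportion ablated and m now the mean ablation time, the mean time of the 12-month visit is 12 + p × m. The difference between arms is (p for control − p for SGLT-2 inhibitor) × m.

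| Ablation time | Control, 50% | SGLT-2 inhibitor, 30% | Difference (months) |
|---|---|---|---|
| All at month 3 | 13.50 | 12.90 | 0.20 × 3 = 0.6 |
| Equally at 3, 6, 9, 12 (mean 7.5) | 15.75 | 14.25 | 0.20 × 7.5 = 1.5 |
| All at month 12 | 18.00 | 15.60 | 0.20 × 12 = 2.4 |

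Patients with a shifted visit: 0.50 × 358 = 179 v 0.30 × 358 = 107.

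If the 50% is read as the overall rate, the arm rates become 0.50/0.80 = 62.5% and 0.60 × 62.5% = 37.5%. The difference is then 0.25 × 3 = 0.75 to 0.25 × 12 = 3.0 months. With equal ablation rates it is 0.

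**Step 3: which outcomes are exposed**
- Exposed: sinus rhythm at 6 and 12 months, EHRA score at 3 to 12 months, and left atrial diameter, NT-proBNP and quality of life at 12 months.
- Not exposed: AF burden, because Table 1 sets its time points separately for patients who did and did not step up.
- Not exposed: the ablation rate, because a clock that starts at ablation cannot change whether ablation took place.

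**The case against.** The strongest reply is that the article already intends two parallel series. The follow-up section fixes the main clock at first prescription and exempts nobody. The Fig 1 caption, the Table 5 footnote and the text below it all speak of an additional year. The 0-month sentence can then be read as month 0 of a session 2 series, and the Discussion explains why such a series exists: recurrence is the primary outcome in each step. Figs 1 and 2, where session 2 visits may be drawn, are not available here.

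This reading is possible, and it means that pooling values from different times is not established. It does not remove the ambiguity. The 0-month sentence speaks of follow-up in general, not of Holter alone. The phrase 12-month final follow-up does not settle it either, because an ablated patient's last visit is 12 months after ablation. Where separate time points were wanted, for AF burden, they were written out; for the pooled outcomes they were not.

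Some stronger inferences fail:
- A reader might infer that the control arm would be measured further from ablation. It would not: on the reset clock every ablated patient, in either arm, has the 12-month visit 12 months after ablation.
- A reader might take 50% v 30% as the trial's own figures. The article gives no step-up rate by arm, and ablation also depends on symptoms and physician judgement.
- A reader might extend the point to the primary outcome. Nothing in the article shows an effect on that comparison.

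**Conclusion.** The point holds as a conflict between stated rules, limited to the pooled secondary outcomes. The article sets month 0 in two places and does not say which applies to an ablated patient's 6- and 12-month assessments.

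Under the literal reset, the 12-month visit of an ablated patient falls 15 to 24 months after randomisation. The difference between arms in mean timing is conditional: 0.6 to 2.4 months under the assumed ablation rates, none if the rates are equal and ablation occurs at similar times. That range describes visit timing only. It has not been translated into bias in any outcome, and the documents give no basis for doing so.

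Severity is moderate. The exposed outcomes are secondary and a benign reading exists, so the point does not need to be treated as a must-fix. It still deserves action because the correction is cheap and assessments missed at month 12 are lost.

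**What to change.** Reconcile the 0-month sentence in Study design and participants with the follow-up section and Table 5 by stating three things:

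1. Month 0 is randomisation or first prescription (name one) for every outcome compared in all participants.
2. The Table 5 assessments are done at 3, 6, 9 and 12 months from that point in everyone, ablated or not.
3. The post-ablation Holter visits form a separate series with their own labels, for example A3, A6, A9 and A12, and are used only for post-ablation outcomes.

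The cost is protocol wording and visit labels in the case report form. Some ablated patients will have extra visits where the two series do not coincide, although Table 5 already schedules the assessments at 3 to 12 months. On the common clock, time since ablation will vary at month 12. That is acceptable for an all-participant comparison, since ablation is part of what follows from allocation, but it should be stated.
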